|---------------------------|-------------------------------------------------------------------------------------------------------------------------------------------------------------------------------------------------------------------------------------------------------------------------------------------------------------------------------------------------------------------------------------------------------------------------------------------------------------------------------------------------------------------------------------------------------------------------------------------------------------------------------------------------------------------------------------------------------------------------------------------------------------------------------------------------------------------------------------------------------------|--------------------------------------------------------------------------------------------------------------------------------------------------------------------------------------------------------------------------------------------------------------------------------------------------------------------------------------------------------------------------------------------------------------------------------------------------------------------------------------------------------------------------------------------------------------------------------------------------------------------------------------------------------------------------------------------------------------------------------------------------------------------------------------------------------------------------------------------------------------------------------------------------------------------------------------------------------------------------------------------------------------------------------------------------------------------------------------------------------------------------------------------------------------------------------------------------------------------------------|-------------------------------------------------------------------------------------------------------------------------------------------------------------------------------------------------------------------------------------------------------------------------------------------------------------------------------------------------------------------------------------------------------------------------------------------------------------------------------------------------------------------------|

976

977 *The above changes to the Protocol and the Statistical Analysis Plan were not substantially different with the*  
978 *initial ones, but could significantly reduce patient risks and improve patient compliance.*  
979

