## 18. Sample Size Estimation

- We design the study as a non-inferiority trial to address the clinical question of whether the no-hydrocortisone protocol is non-inferior to the traditional regimen regarding the incidences of new-onset acute AI during perioperation after surgery for PAs in patients with an intact HPA-axis.
- The sample size is calculated based on the between-group comparison of the primary outcome (the incidences of new-onset AI during perioperation) to detect a 10% difference on the incidence of AI (as indicated by the 95% CI) during perioperation of pituitary surgery. The non-inferiority margin ( $\delta$ ) is thus set as 0.1.
- The calculation formula for qualitative data in non-inferiority trials ( $N=2 \times [U\alpha + U\beta]^2 \times P[1-P]/\delta^2$ ) is used, with  $\alpha$  set at 0.05 and  $\beta$  at 0.2.
- According to the published literature (DOI: 10.3171/2019.11.JNS192381; DOI: 10.1093/neuros/nyy479) and our preliminary observation, we set  $\sigma$  as 0.2.
- Assuming a 10% loss to follow-up, the sample size is finally determined as 218 in each trial group and 436 in total.

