## 20. Statistical Analysis Plan

- This is a single-center, parallel-group, non-inferiority, randomized, controlled trial.
- We follow the CONSORT guideline for reporting the result of this trial.
- Qualitative data are to be presented as numbers, percentages, and 95% CI, and quantitative data are to be presented as means and standard deviations.
- Analyses of the primary, secondary, and other outcomes will be performed by calculating the 95% CI of the difference: mean incidence (no-hydrocortisone group) – mean incidence (hydrocortisone group).
- Non-inferiority is identified if the upper limit of the 95% CI is smaller than the margin of 10 percent points.
- We assess superiority for the outcomes in which the non-inferiority is achieved.
- Post hoc subgroup analyses and prognostic analyses will be performed for the primary and secondary outcomes.
- We use the receiver operator characteristic (ROC) curve to detect the cut-off value of baseline serum cortisol in predicting early and late postoperative AI.
- The student's t-test will be used for comparisons of continuous variables and chi-squared test for categorical variables.
- A P value < 0.05 is considered statistically significant.

691     **21. Randomization sequence**

| VAR00001 | Random | Group | VAR00001 | Random | Group | VAR00001 | Random | Group |
|----------|--------|-------|----------|--------|-------|----------|--------|-------|
| 1        | 0.87   | 2     | 31       | 0.54   | 2     | 61       | 0.26   | 1     |
| 2        | 0.34   | 1     | 32       | 0.58   | 2     | 62       | 0.91   | 2     |
| 3        | 0.60   | 2     | 33       | 0.96   | 2     | 63       | 0.20   | 1     |
| 4        | 0.04   | 1     | 34       | 0.21   | 1     | 64       | 0.23   | 1     |
| 5        | 0.56   | 2     | 35       | 0.41   | 1     | 65       | 0.34   | 1     |
| 6        | 0.91   | 2     | 36       | 0.74   | 2     | 66       | 0.08   | 1     |
| 7        | 0.94   | 2     | 37       | 0.76   | 2     | 67       | 0.41   | 1     |
| 8        | 0.85   | 2     | 38       | 0.53   | 2     | 68       | 0.57   | 2     |
| 9        | 0.47   | 2     | 39       | 0.99   | 2     | 69       | 0.46   | 1     |
| 10       | 0.71   | 2     | 40       | 0.32   | 1     | 70       | 0.30   | 1     |
| 11       | 0.57   | 2     | 41       | 0.30   | 1     | 71       | 0.60   | 2     |
| 12       | 0.55   | 2     | 42       | 0.34   | 1     | 72       | 0.13   | 1     |

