| Definition of diabetes mellitus                                           | A random reading of blood sugar level more than 200 mg/dL (11.1 mmol/L), or a reading after two hours (after OGTT) over 200 mg/dL (11.1 mmol/L).                                                                                                                                                                            | A fasting plasma glucose level ≥ 126 mg/dl (7.0 mmol/l) or the 2-h plasma glucose value ≥ 200 mg/dL (11.1 mmol/L) after the oral glucose tolerance test.                                                                                                                                                                                                                                                                                                       | We modified the definition of diabetes mellitus according to the current criteria (Classification and diagnosis of diabetes. Diabetes Care 2015;38 Suppl: S8-S16) and reevaluated the incidences accordingly as presented in the article.                                                                                                                                                                                                 |

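### The 10-point margin set for acute AI is applied to every outcome, and each outcome that passes is then tested for superiority with no multiplicity control

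*Supplement*

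**What the plan says.** Section 18 (Sample Size Estimation) ties the design to one outcome: "The sample size is calculated based on the between-group comparison of the primary outcome (the incidences of new-onset AI during perioperation"). The margin of 0.1 is introduced there, "with $\alpha$ set at 0.05 and $\beta$ at 0.2", and the planning value is given as "we set $\sigma$ as 0.2".

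Section 20 (Statistical Analysis Plan) widens the scope. The confidence-interval analysis covers all three tiers of outcome: "Analyses of the primary, secondary, and other outcomes will be performed by calculating the 95% CI of the difference". The decision rule names no outcome: "Non-inferiority is identified if the upper limit of the 95% CI is smaller than the margin of 10 percent points". The next step is in the plural: "We assess superiority for the outcomes in which the non-inferiority is achieved". The only significance threshold is "A P value < 0.05 is considered statistically significant".

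Section 16 lists seven outcomes that are incidences or rates: acute AI (primary), late AI (secondary), and diabetes mellitus, diabetes insipidus, electrolyte disturbance, deep venous thrombosis and decreased bone density (other). The final version gives no margin specific to any non-primary outcome, no testing order, no multiplicity adjustment and no statement that these outcomes are supportive only.

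**The concern.** A margin in percentage points has meaning only against the rate it was set for. Ten points against an assumed 20% rate of acute AI is one judgement; ten points against a complication seen in one or two patients per hundred is quite another, because the rate can multiply several times before the upper confidence limit reaches 10 points. Section 12 frames the trial as a test of whether withholding hydrocortisone is safe, so a non-inferior label on deep venous thrombosis, for example, would be read as reassurance.

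The second issue is the superiority step. It is repeated over up to seven outcomes at the same threshold, so a claim that withholding is superior on some outcome can arise by chance well above the rate expected of a single test.

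**Working it through.** **Inputs.** From Section 18: margin 0.10, planning value 0.2, alpha 0.05, beta 0.2, 10% loss, 218 per group. From Section 20: upper 95% limit below 10 points, then superiority at P < 0.05. From Section 16: seven outcomes. Evaluable number per arm: 218 × 0.9 = 196. Rates for the non-primary outcomes are not in the documents and are assumed below. The SAP does not name the interval method; Wald is used, with Newcombe as a check.

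**Step 1: reproduce the plan's own figure.** N = 2(Uα + Uβ)² P(1 − P)/δ². With P = 0.2, one-sided alpha 0.05 and 80% power: 2 × (1.645 + 0.842)² × 0.16/0.01 = 197.8, so 198 per arm; 198 × 1.1 = 218. The stated number is reproduced, which confirms that the 0.2 enters as the event rate of acute AI and that the margin belongs to that outcome. (Two-sided alpha 0.05 gives 252 before loss and does not reproduce it.)

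**Step 2: the rule on observed counts.** Upper limit = (pT − pC) + 1.96 √[pC(1 − pC)/n + pT(1 − pT)/n], where T is no hydrocortisone and C is hydrocortisone. Take 2/196 on C and 14/196 on T:
- difference 12/196 = 0.0612;
- standard error √(0.0102 × 0.9898/196 + 0.0714 × 0.9286/196) = 0.0197;
- upper limit 0.0999, so the outcome passes.

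The chi-squared test on the same counts uses the pooled rate 16/392 = 0.0408: z = 0.0612/√(0.0408 × 0.9592 × 2/196) = 3.06, so P is about 0.002. A sevenfold, clearly significant excess is thus called non-inferior. (By Newcombe, 12/196 is the largest count that passes against 2/196.)

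**Step 3: probability of passing.** Sum the product of the two binomial probabilities over all pairs of counts whose upper limit is below 0.10, with n = 196 per arm. The last column adds the condition that the chi-squared test shows T significantly worse.

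| True rate, C vs T (assumed) | Passes, Wald | Passes, Newcombe | Passes (Wald) and significantly worse |
|---|---|---|---|
| 1% vs 4% | 98% | 95% | 46% |
| 1% vs 5% | 91% | 83% | 58% |
| 2% vs 6% | 84% | 76% | 38% |
| 3% vs 6% | 90% | 86% | 20% |
| 5% vs 10% | 48% | 44% | 2% |
| 20% vs 20% | 70% | 70% | – |
| 30% vs 30% | 58% | 59% | – |

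With all 218 per arm evaluable, 1% vs 5% passes 93% of the time (Newcombe 87%), and 66% of the time it passes while significantly worse.

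**Step 4: superiority.** A false claim favouring withholding has probability 0.05/2 = 0.025 per outcome when there is no true difference. The non-inferiority step does not lower this: an interval lying wholly below zero also lies below 10 points. At equal rates of 20% or 30% the favourable error is still 2.5%, although only 70% or 58% of trials pass. For independent outcomes:
- seven outcomes: 1 − 0.975⁷ = 16.2%;
- six non-primary outcomes: 1 − 0.975⁶ = 14.1%.

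For rare, discrete outcomes (1–5%) the per-test error is about 2.0–2.4%. At 2.0% throughout, seven outcomes give 1 − 0.98⁷ = 13.2%. Positive correlation lowers it further.

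**The case against.** The strongest defence is that the trial's claim rests on acute AI alone. Section 14 states the hypothesis for it, Section 18 sizes the trial on it, and Section 16 already ranks outcomes as primary, secondary and other. Nothing here changes the primary margin, analysis or sample size, and the documents nowhere call the other outcomes confirmatory. That stands, and it limits the severity. It does not remove the point, because Section 20 assigns labels to those outcomes all the same. Reading the 10-point rule as primary-only is hard to square with the plural in the superiority sentence.

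Rarity is an assumption. Electrolyte disturbance is any out-of-range sodium, potassium or calcium over three months and may be common. A reader might infer that the rule is empty for every outcome; the 5% vs 10% and equal-30% rows show otherwise.

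The harm examples also run in one direction, whereas Section 14 expects withholding to spare patients steroid-related events. For such outcomes the more relevant error is a false superiority claim. That is fair, and Step 4 covers it.

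Three stronger readings are not supported:
- A reader might quote 1 − 0.95⁷ = 30% as the false-superiority risk. That counts results significantly worse under withholding, which are not superiority claims.
- A reader might infer that moving from non-inferiority to superiority inflates error by itself. On one outcome it does not; the repetition over outcomes does.
- A reader might hold the redefinition of diabetes mellitus and diabetes insipidus in the Summary of Changes against these outcomes. A change between versions is no fault in itself, and the Section 16 definitions are explicit.

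**Conclusion.** The point holds as a should-fix. Section 20 carries a margin set for acute AI at 20% over to six outcomes for which it was never justified. For any outcome with an assumed 1–3% rate on hydrocortisone, true increases of two- to fivefold pass 84–98% of the time by Wald and 76–95% by Newcombe, with 196 per arm. At 1% vs 5% the plan would more likely than not (58%) attach a non-inferior label to a result that its own chi-squared test calls significantly worse. For common outcomes this laxity is absent.

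The superiority step adds a chance of up to about 16% of at least one false claim for withholding over seven outcomes (14% over the six non-primary ones). These are upper figures that assume independence and no true differences. The sizes depend on assumed rates; the mismatch in scope between Sections 18 and 20 does not. The documents do not support extending the criticism to the acute-AI conclusion.

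**What to change.** In Section 20, restrict the 10-point non-inferiority rule, and the superiority test that follows it, to acute AI. On that single outcome the two steps need no alpha adjustment.

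Report late AI, diabetes mellitus, diabetes insipidus, electrolyte disturbance, deep venous thrombosis and decreased bone density as risk differences with 95% CIs, by Newcombe or Miettinen-Nurminen where counts are small. Describe them as supportive, with no non-inferiority or superiority label.

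If a formal claim on late AI is wanted, justify a margin for it and test it directly after acute-AI non-inferiority. It should not sit behind acute-AI superiority: Section 18 plans on one common rate, under which that superiority test succeeds only about 2.5% of the time, so late AI would almost never be tested. The place of the acute-AI superiority test in that sequence should then be written down too.

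The cost is SAP wording. No patients, data or procedures are added; the sponsor gives up the labels on the non-primary outcomes.

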## 19. Randomization, Masking, and Data Collection

- Patients are to be randomly assigned, in a 1:1 ratio, to undergo perioperative administration of hydrocortisone or not to undergo such administration.
- The randomization sequence will be generated before patient recruitment using SPSS Statistics software with a fixed model.
- The blinded assignment will be performed.
- The study staff who collected trial data and those who assess the outcomes, the investigators, and study participants and their families are all blinded to group assignment before unblinding.
- The executive nurses and neurosurgical residents who allocated drugs or placebos know the treatment assignment and keep secret.
- Data collection: Serum cortisol level is evaluated at baseline (8 am), on the OD (three timings: after anesthesia induction, OD1; after nasal mucosa incision, OD2; and after tumor removal, OD3), POD1 (8 am)

and POD2 (8 am), and in the 3rd postoperative month (POM3, 8 am). Serum ACTH level is evaluated before surgery (8 am, baseline), on POD1 (8 am) and POD2 (8 am), and in POM3 (8 am).

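### The primary risk difference is valid but ignores baseline 8 am cortisol; pre-specified adjustment is an optional, low-cost gain in precision, probably small

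*Supplement*

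**What the plan says.** Section 20 (final Statistical Analysis Plan) states: "Analyses of the primary, secondary, and other outcomes will be performed by calculating the 95% CI of the difference", taken as no-hydrocortisone minus hydrocortisone. The decision rule is "Non-inferiority is identified if the upper limit of the 95% CI is smaller than the margin of 10 percent points". Chi-squared tests are planned for categorical variables. No model, covariate or stratified analysis is named for the primary outcome.

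Section 19 schedules the relevant covariate: "Serum cortisol level is evaluated at baseline (8 am". It describes 1:1 allocation and names no stratification factor. Section 20 also plans a receiver operating characteristic (ROC) curve to find the "cut-off value of baseline serum cortisol in predicting early and late postoperative AI". That analysis is not linked to the primary comparison.

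Section 16 defines AI as 8 am cortisol below 5 µg/dl plus at least one symptom. The baseline value is therefore an earlier measurement of the outcome's own laboratory component.

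For the sample size, section 18 works "with $\alpha$ set at 0.05 and $\beta$ at 0.2", says the margin "is thus set as 0.1", and gives the remaining input as "and our preliminary observation, we set $\sigma$ as 0.2".

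**The concern.** When a baseline variable related to the outcome is already measured, a covariate-adjusted estimate of the same marginal risk difference usually has a narrower confidence interval. It also accounts for whatever imbalance in that variable arises by chance. The plan measures such a variable and thinks it worth studying as a predictor, but leaves it out of the one comparison that decides the trial.

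If the AI rate is as high as the sample-size calculation assumes, power against the stated decision rule is modest, so some precision would be useful. The choice has to be made in advance: an adjusted result chosen after unblinding would carry little weight.

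**Working it through.** **Inputs from the plan.** Margin 0.10; alpha 0.05 with sidedness not stated; beta 0.2; event rate P = 0.2 (the text labels it sigma, but only reading it as P reproduces the sample size); 10% loss; 218 per arm; decision by the upper limit of a 95% CI, read as two-sided.

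**Input that the plan does not give.** The predictive strength of baseline cortisol. AUC values of 0.60 to 0.80 are assumed.

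**Step 1: the plan's own figure.** N = 2(Uα + Uβ)² P(1 − P)/δ².
- One-sided 0.05: 2 × (1.645 + 0.842)² × 0.16/0.01 = 197.8, so 198; × 1.10 = 218. This reproduces the plan.
- One-sided 0.025, which is what a two-sided 95% CI implies: 251.2, so 252 evaluable, or 280 after dividing by 0.90. This does not.

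**Step 2: unadjusted power under the stated rule.** Evaluable n = 218 × 0.90 = 196 per arm. SE = √(2 × 0.16/196) = 0.0404. Power = Φ(0.1/0.0404 − 1.96) = 69.7%. With all 218 analysed it is 74.2%.

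**Step 3: variance removed by adjustment.** Let V = P(1 − P) in each arm, N the total number of patients, and R² the share of outcome variance explained by cortisol.
- Unadjusted variance: 4V/N.
- Cortisol predicts equally in both arms: 4V(1 − R²)/N.
- Cortisol predicts in one arm only: [2V(1 − R²) + 2V + R²V]/N = 4V(1 − R²/4)/N, so a quarter of the reduction.

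R² comes from a logistic risk on a standard normal covariate with a marginal rate of 0.20. Power is Φ(0.1/(SE√(1 − reduction)) − 1.96).

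| Assumed AUC | R² | Power, both arms | Reduction, one arm only | Power, one arm only |
|---|---|---|---|---|
| 0.60 | 0.021 | 70.6% | 0.5% | 69.9% |
| 0.66 | 0.054 | 72.1% | 1.4% | 70.3% |
| 0.705 | 0.092 | 73.8% | 2.3% | 70.7% |
| 0.745 | 0.134 | 75.8% | 3.3% | 71.1% |

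In the last three rows, prediction in both arms equals 196/(1 − R²) = 207, 216 or 226 patients per arm, that is 11, 20 or 30 more than 196. Returning to about 80% power by adjustment alone would need R² of about 0.21 (AUC about 0.80) in both arms.

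**Step 4: a lower event rate.** At P = 0.10, unadjusted power at 196 per arm is 91.0%. The same three covariate strengths remove 3.3%, 6.0% and 9.2% of the variance if cortisol predicts in both arms, and power becomes 91.9% to 93.4%. At P = 0.05 unadjusted power exceeds 99%.

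**Step 5: simulation of the standardised logistic estimate** (4,000 trials per setting, 196 per arm, P = 0.2). With AUC about 0.70 in both arms, power went from 70.3% to 74.2%. With the true difference at the margin, false non-inferiority was 2.5% unadjusted and 2.6% adjusted, so the error rate is kept. With prediction in the no-hydrocortisone arm only, power went from 69.6% to 70.8%.

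**The case against.** The strongest objection is that nothing here is a defect. An unadjusted risk difference with a 95% CI is a sound primary analysis in a randomised trial. A reader might infer that chance imbalance in cortisol biases it. It does not: the interval already allows for chance imbalance on average, and its coverage is unaffected. This stands in full.

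Second, the documents give no AUC. A reader might take the ROC plan as evidence that cortisol predicts well, but it shows only that the question is of interest. Eligibility requires an intact HPA axis and excludes preoperative AI (section 17), which plausibly narrows the range of baseline values. This also stands.

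Third, the design works against equal prediction in the two arms. The cortisol values that define early AI are taken at 8 am on postoperative days 1 and 2 (section 19), when the comparator arm is on intravenous hydrocortisone (section 15). Measured cortisol there plausibly reflects the drug more than the patient's own axis. The one-arm columns of the table are therefore the likelier case.

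Fourth, a logistic model can fail if one arm has few or no events. This is a real drawback, though a fallback rule deals with it.

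The suggestion survives all four: the covariate is already scheduled, the estimand and margin do not change, and no calculated or simulated case lost power.

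**Conclusion.** An optional, low-cost improvement in efficiency. It corrects no bias. At a 20% AI rate with 196 per arm, the benefit is about 2 to 6 points of power if baseline cortisol has AUC 0.66–0.75 in both arms, and about 0.5 to 1.5 points if it predicts only without hydrocortisone. At a 10% rate it is at most about 2 points. All of these rest on assumed AUCs and on reading the decision rule as a two-sided 95% CI.

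A reader might infer that adjustment would restore the planned 80% power. The figures do not support that. The gap between 80% and about 70% comes from sizing the trial at one-sided 0.05 and then deciding by a 95% CI. That inconsistency must be settled separately. The 70% is itself derived, not stated in the plan, and holds only at a rate near 20%.

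**What to change.** Before unblinding, add to section 20:

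- The primary estimate is the standardised (g-computation) risk difference from a logistic model with arm and continuous baseline 8 am cortisol, with a robust 95% CI, compared with the same 10-point margin. Do not use an odds ratio, which would change the estimand, or a cut-off derived from the trial's own ROC curve.
- If an arm has no events or the model does not converge, the unadjusted difference with a score-type 95% CI is the primary result.
- The unadjusted difference is reported as a sensitivity analysis in every case.
- The functional form for cortisol and the handling of a missing baseline value are stated.

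The cost is a short paragraph in the plan, slightly more analysis work and one fallback rule. It needs no extra patients and no new measurements.

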### 3) Other Outcome Measures:

- Rate of newly-developed diabetes mellitus [Time Frame: During the first 3 postoperative months]

*Diabetes mellitus:* A random reading of blood sugar level more than 200 mg/dL (11.1 mmol/L), or a reading after two hours (after OGTT) over 200 mg/dL (11.1 mmol/L).

- Rate of newly-developed diabetes insipidus [Time Frame: During the first 3 postoperative months]  
*Diabetes insipidus*: Urine volume > 300ml for more than 3h or > 6 liter per day, specific gravity of urine <1.003, and serum sodium levels > 145 mmol/L.
- Concentration of blood electrolytes [Time Frame: At the 3rd postoperative month]  
 The level of Na+, K+, and Ca++ in the blood.
- Concentration of blood cells [Time Frame: At the 3rd postoperative month]  
 Numbers of erythrocytes, leukocytes, neutrophils, lymphocytes, thrombocytes in the blood.
- Percentage of blood cells [Time Frame: At the 3rd postoperative month]  
 Percentage of neutrophils, monocytes, lymphocytes of the leukocytes.
- Concentration of indexes of coagulation function [Time Frame: At the 3rd postoperative month]  
 Prothrombin time, activated partial thromboplastin time, and thrombin time.
- Level of international normalized ratio [Time Frame: At the 3rd postoperative month]  
 Level of international normalized ratio.
- Level of D-Dimer [Time Frame: At the 3rd postoperative month]  
 Level of D-Dimer.
- Rate of deep venous thrombosis [Time Frame: During the first 3 postoperative months]  
*Deep venous thrombosis* is detected by ultrasound.
- Rate of other complications [ Time Frame: During the first 3 postoperative months]  
 Decreased bone density, osteoporosis, fracture, acne, and infections.

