## 3) Other Outcome Measures:

- Rate of newly-developed **diabetes mellitus** [During the first 3 postoperative months]

*Diabetes mellitus:* A fasting plasma glucose level  $\geq 126 \text{ mg/dl}$  ( $7.0 \text{ mmol/l}$ ) or the 2-h plasma glucose value  $\geq 200 \text{ mg/dL}$  ( $11.1 \text{ mmol/L}$ ) after the oral glucose tolerance test.

- Rate of newly-developed **diabetes insipidus** [During the first 3 postoperative months]

*Diabetes insipidus:* Urine volume  $> 300 \text{ ml/h}$  for more than 3 consecutive hours, urine specific gravity  $< 1.005$ , and serum sodium  $> 145 \text{ mmol/l}$ .

- Rate of **electrolyte disturbance** [During the first 3 postoperative month]

*Electrolyte disturbance* is defined as lower-than- or higher-than-normal levels of serum sodium ( $135\text{-}145 \text{ mmol/l}$ ), potassium ( $3.5\text{-}5.5 \text{ mmol/l}$ ), and calcium ( $2.13\text{-}2.70 \text{ mmol/l}$ ).

- Rate of **deep venous thrombosis** [During the first 3 postoperative months]

*Deep venous thrombosis* is detected by the ultrasound.

- Rate of **decreased bone density** [During the first 3 postoperative months]

*Decreased bone density* is detected by the dual-energy x-ray absorptiometry.

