| Definition of diabetes insipidus      | Urine volume > 300ml for more than 3h or > 6 liter per day, specific gravity of urine <1.003, and serum sodium levels > 145 mmol/L.                                                                                                                                                                                                                                                                                          | Urine volume > 300 ml/h for more than 3 consecutive hours, urine specific gravity < 1.005, and serum sodium > 145 mmol/l.                                                                                                                                                                                                                                                                                                                                                                                                                                                           | We modified the definition of diabetes insipidus according to the current criteria (Postoperative diabetes insipidus: how to define and grade this complication? Pituitary 2021;24(2):284-291) and reevaluated the incidences accordingly as presented in the article. |

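### The diabetes mellitus and diabetes insipidus criteria appear to have been replaced after incidences had been evaluated, and the final plan neither dates the change nor analyses the initial criteria alongside

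*Supplement*

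**What the plan says.** Section 5 of the initial protocol and Section 16 of the final protocol both list new DM and new DI over the first three postoperative months under other outcome measures.

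The initial DM definition accepted a random glucose above 200 mg/dL or a 2-hour value above 200 mg/dL after glucose loading. The initial DI definition began "Urine volume > 300ml for more than 3h or > 6 liter per day, specific gravity of urine <1.003" and also required serum sodium above 145 mmol/L. Section 16 of the final protocol gives only the replacement criteria.

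The Summary of Changes explains both replacements as a move to current criteria and cites a source for each. The DM row adds "and reevaluated the incidences accordingly as presented in the article", and the DI row uses the same words. No other row of the log does. The row on the primary endpoint says that a threshold was specified and a period defined, and the electrolyte row says that definitions were detailed.

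Section 20 of the final plan analyses primary, secondary and other outcomes alike, by the 95% CI of the difference in incidence. It then adds "We assess superiority for the outcomes in which the non-inferiority is achieved", with significance at P < 0.05. It plans no analysis under the initial DM or DI criteria. The log closes by saying that the changes "were not substantially different with the" initial ones.

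**The concern.** That a definition changed between versions is not the point. The point is what the latest plan does with a definition that, on the log's own wording, was settled after outcome data had been classified once. Sections 16 and 20 treat the new criteria like any other outcome definition. Section 20 marks subgroup and prognostic analyses as post hoc but puts no such mark on the redefined outcomes, and it lets them carry a superiority claim.

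Two harm comparisons are at stake. Section 14 gives avoidance of steroid-related adverse events as part of the reason for withholding hydrocortisone, so a lower DM rate would support the experimental arm. DI is one of the few other complications that the final plan defines. If a between-arm difference on either depends on which definition is used, a reader of the final plan has no means of finding out.

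**Working it through.** **Inputs.** The criteria come from Section 5 (initial) and Section 16 (final), the timing from the two Summary of Changes rows, and the test rules from Section 20. The plan gives no expected incidence, power or sample size for DM or DI, so there is no stated figure to reproduce.

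**Step 1: do the case sets differ?**

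| Outcome | Initial (Section 5) | Final (Section 16) | Effect on who counts |
|---|---|---|---|
| DM, non-OGTT route | random glucose > 200 mg/dL | fasting glucose ≥ 126 mg/dL | one route lost, one gained |
| DM, OGTT route | 2-h value > 200 mg/dL | 2-h value ≥ 200 mg/dL | almost the same |
| DI, volume | > 300 ml over more than 3 h (no hourly rate printed), or > 6 L/day | > 300 ml/h over more than 3 consecutive h | daily route lost: narrower |
| DI, specific gravity | < 1.003 | < 1.005 | wider |
| DI, sodium | > 145 mmol/L | > 145 mmol/L | unchanged |

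For each outcome, some patients could be cases under one definition and not the other. The changes pull in opposite directions, so the net effect on incidence cannot be derived from the documents, and neither can its effect on the difference between arms. The log's assurance that little changed therefore cannot be checked for these two outcomes.

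**Step 2: what does the log establish about timing?** Re-evaluation implies a previous evaluation, and the reference to the article places the second one at or near reporting. No date, data-lock status or blinding status is given. For DM the cited criteria carry the year 2015, while the initial protocol's sample-size section already cites an identifier containing 2019.11. The DM source therefore predates the initial plan, and newly available criteria do not explain the timing. For DI the cited source is from 2021, so that explanation is more plausible.

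**Step 3: how large could the effect be, hypothetically?** Suppose there is no true difference, both definitions of one outcome are tested at two-sided 0.05, and whichever is significant is the one reported. With test statistics Z₁ and Z₂ correlated at r:

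P(at least one significant) = 1 − P(|Z₁| < 1.96 and |Z₂| < 1.96).

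At r = 0 this is 1 − 0.95² = 0.0975. From the bivariate normal distribution, with r assumed because the documents give no value:

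| r | Either direction (nominal 5%) | One chosen direction (nominal 2.5%) |
|---|---|---|
| 0.5 | 9.1% | 4.5% |
| 0.7 | 8.4% | 4.2% |
| 0.9 | 7.0% | 3.5% |
| 0.99 | 5.7% | 2.8% |

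These are per-outcome figures and upper bounds. They apply only if the definition was chosen on its result, which the documents do not show.

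**The case against.** The strongest reply is that the change is disclosed. The log sets old and new criteria side by side with a reason and a published source for each, and the whole initial protocol is reproduced. Section 19 says that data collectors, outcome assessors and investigators stay blinded until unblinding. A blinded or pooled reclassification before that point would fit the log's words just as well. The initial DI volume criterion also lacks a rate unit, which the final text repairs. The article that the log refers to is not part of the documents and may report both definitions.

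Much of this stands. A reader might infer that the sponsor saw both definitions tabulated by arm and kept the more favourable one. The documents do not support that inference: they do not say whether the first evaluation was by arm, complete or unblinded, and nothing shows that results drove the choice. For the same reason the 7–9% range is not an estimate of error in this trial. The two definitions share components (the glucose-load route for DM, the sodium condition for DI), so the correlation could be high and the inflation small. A rule forbidding any claim unless both definitions agree would also go too far, since it would give a veto to a DI criterion printed without a rate.

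What the reply does not remove is the gap in the final plan. Disclosing that criteria changed is not the same as stating when they changed relative to unblinding, and printing the initial criteria is not the same as planning an analysis under them. A sound clinical reason for new criteria does not make them pre-specified.

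**Conclusion.** The point holds as a reporting and sensitivity-analysis gap for two outcomes. The log indicates that DM and DI incidences had already been evaluated when the criteria were replaced. The final plan does not date the change, analyses only the new criteria without a post hoc label, and opens superiority claims on them. The conclusion rests on the ordinary meaning of re-evaluating incidences and on the absence of any date or blinding statement.

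Its size is limited. The primary and secondary outcomes, the margin and the sample size are untouched. The direction of any effect on DM or DI cannot be derived, and the error-inflation figures are hypothetical bounds. It is a cheap improvement and does not threaten the trial's main conclusion.

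**What to change.** In Section 20 of the final plan:

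- Report DM and DI by arm under both the initial criteria (Section 5) and the final criteria (Section 16), with counts, risk difference and 95% CI side by side, as a sensitivity analysis. Read the initial DI volume limit as ml/h and say that this reading was adopted.
- State the date on which each definition was changed and whether it preceded unblinding. Label the final-criteria analyses as post hoc unless the change is shown to predate unblinding.
- Treat any superiority result on DM or DI as exploratory.

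The cost is one extra table. The log implies that the initial-criteria incidences were already evaluated. However, the data-collection list in Section 19 names only cortisol and ACTH, so the table should give the number of patients assessable under each definition. The downside for the sponsor is that a DM or DI claim may look less favourable if the two definitions disagree. Sample size, trial conduct and the primary analysis do not change.
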